### Interventions

#### Mindfulness-based interventions (MBIs)

The two MBIs (face-to-face and Internet delivered) are composed of an initial face-to-face group (6-8 participants) session to introduce the therapeutic modules, explain how mindfulness can help patients with their problem, and motivate them to change. In the case of online patients, the therapist will also explain how to enter the web page where the therapeutic modules are located. Thus, both conditions are composed of four modules, face-to-face or online, depending on the assigned condition. Regardless of the condition, all the patients will receive their corresponding TAU.

- “*Face-to-face MBI” sessions* will be carried out in a group format (between 6 and 8 participants) and with weekly sessions lasting 90 min each for 4 weeks. The therapist will explain the different modules and how to do the mindfulness exercises. The mindfulness activities will be performed in the sessions, and then participants will have to practice at home. All the materials will be delivered in print form, except the audios, which will be sent by e-mail. However, the audios will also be transcribed in the printed modules. Module contents are the same as those in the online intervention. These contents have been adapted from an online format previously used [10] to a traditional format for their application in this study. If a participant does not attend a session, the corresponding materials will be delivered to him/her, and s/he will be able to ask any questions about them in the next session.

- “*Internet-based MBI”* will be carried out online and individually through a web platform (https://www.psicologiaytecnologia.com/) where participants will have to introduce a login and a password to enter their corresponding profiles. The duration of each module will be approximately 60-90 min, depending on the participant’s pace and time availability, and the estimated program duration for most people will be between 4 and 8 weeks [10]. Some meta-analyses have shown that attrition rates are higher when no therapist support is provided to patients in Internet-based programs [21, 42]. For this reason, when the patients complete the second module (halfway through the program), they will receive a phone call from the therapist who will monitor their progress and motivate them to continue and adhere to the program. However, no additional therapeutic content will be offered.

Before the therapeutic modules, there is an *introductory module* (M0) with basic information about emotional disorders, the protocol contents, the importance of evaluation and registers, and ambivalence as a natural part of change, as well as an exercise where the participant fills in a table with the costs and benefits of the change process. This module is carried out face-to-face in both treatment conditions before the pre-treatment assessment and the intervention, and it is presented individually to the Internet-based MBI arm and in group format to the face-to-face MBI arm.

The therapeutic modules are oriented toward working on different formal psychological mindfulness practices that can help to decrease depressive symptomatology. These practices emphasize thought management, acceptance, values orientation, and compassion over a short period of time. For this reason, a brief intervention is proposed, composed of four modules (a brief description of each module is presented below).

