### Study population, recruitment, and eligibility criteria

This randomized controlled clinical trial will be conducted from the Health Center of Arrabal in Zaragoza (Spain). Participants will be adult PC outpatients attended to by their corresponding General Practitioners (GP), and they will be recruited by GPs working in the different Health Centers in Zaragoza (Spain). The researchers who manage the study will go to the different Health Centers to explain the study and eligibility criteria to the GPs, and they will give them an information sheet containing the study characteristics.

When a GP identifies a potential patient, s/he will explain the study to him/her and inform him/her that s/he can refuse to participate or withdraw from the study at any time, without any negative effects on their professional relationship or on future treatments that might be offered to the participant in PC. If the patient is interested, s/he will have to come to the Arrabal Health Center to clarify any doubts about the study and sign an informed consent form. Then, the patient will undergo a clinical interview and fill out the paper-and-pencil screening survey describing his/her sociodemographic and clinical characteristics. This first data collection and screening will be performed by specially trained psychologists with the objective of assessing whether the participants meet the eligibility criteria to participate in the study. If the participant meets the inclusion criteria, an independent researcher will implement randomization by telephone to avoid predictability.

Inclusion criteria will be as follows: a) older than 18 years; b) DSM-5 diagnosis of Major Depression or Dysthymia or mild or moderate depression, expressed as a score between 5 and 14 on the Patient Health Questionnaire (PHQ) [35]; c) depressive symptoms present for at least 2 months; d) having a computer and Internet at home; e) being able to read and understand the Spanish language; and f) willingness to participate in the study and sign the written informed consent form.

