### Sample size

The sample size estimation was based on testing whether the trend in the change is different between the intervention groups throughout the 4 time points. Firstly, we assumed that MBI groups would be able to present moderately high effects, compared to “TAU alone”, on the BDI-II at post-treatment. To operationalize this, we considered a standardized difference between arms on the main outcome of d = 0.7, which corresponds to the average effect observed in ten studies comparing MBIs with different wait-list conditions [36] and surpasses the 0.5 standard deviation criterion considered clinically relevant in previous studies [37, 38]. A preceding study by our research group with mild or moderate depressed patients in a similar Spanish PC setting found BDI-II means and standard deviations (SDs) of 22 and 5, respectively [20]. The inclusion criteria used in this study restricted the entry of mild or moderate depressed patients, thus reducing the SD compared to the general population and presenting a less skewed distribution of the data, as we predict will occur in the present study. The effect size referred to above corresponds to a difference of 3.5 points, which implies a reduction of slightly more than 15% in the BDI-II scale used. According to the GLIMMPSE v2.0.0 – time x group interaction in a general linear repeated measures (RM) design – and GPower v3.1.9.4 – ANOVA test for RM within-between interaction – statistical tools, considering the referred difference between the “face-to-face MBI + TAU” vs. “TAU alone” groups of depressed patients, which corresponds to a partial eta square value of roughly 0.09 and an effect size f of 0.31, with a common mean at baseline of 22, a mean at post-test of 16 and 19.5 respectively, and a mean at post-test of 17 for the “Internet delivered MBI + TAU” condition, and assuming a one point reduction in each group at each following time point, a baseline correlation of 0.6 and a decay rate of 0.35, assuming a common SD of 5, a 5% significance level, a statistical power of 80% using a 1:1:1 ratio, and an univariate approach to RM with Greenhouse-Geisser correction [39], we needed 33 subjects in each group. Because we expected a dropout rate of approximately 20% [40], we inflated the numbers to reach a total sample size of 120 patients, 40 per arm [41].

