### Instruments

The evaluations will be performed at screening, baseline, post-treatment, and 6- and 12-month follow-ups. All variables and assessment periods of the study can be found in Table 1. Scores on depression, negative and positive affect, and opinions about the modules will also be obtained after each completed module in the face-to-face and Interned-based MBIs. Participants in the TAU group will report their general opinion about the treatment as usual received at the end of the program.

**Table 1 Tab1:** Study outcomes

Instruments	Assessment Area	Time of assessment^a^
Sociodemographic	Gender, age, marital status, education, occupation, economical level.	Screening
MINI	Psychiatric diagnosis	Screening
PHQ-9	Severity of depression	Screening, post-module, post-treatment and follow-ups
CSRI	Health and social services use	Screening and 12-month follow-up
BDI-II	Severity of depression	Baseline, post-treatment and follow-ups
SF-12	Health-related quality of life	Baseline, post-treatment and follow-ups
EQ-5D	Health-related quality of life	Baseline and follow-ups
PANAS	Positive and negative Affect	Baseline, post-modules and follow-ups
FFMQ	Facets and factors of mindfulness	Baseline and follow-ups
PHI	Remembered and experienced well-being	Baseline and follow-ups
ETS	Treatment expectations	Baseline
OTS	Treatment opinions	Post-treatment

*MINI* Mini-International Neuropsychiatric Interview, *PHQ-9* Patient Health Questionnaire-9, *CSRI* Client Service Receipt Inventory, *BDI-II* Beck Depression Inventory-II, *SF-12* Short Form-12 Health Survey, *EQ-5D* EuroQoL-5D Questionnaire, *PANAS* Positive and Negative Affect Scale, *FFMQ* Five Facet Mindfulness Questionnaire, *PHI* Pemberton Happiness Index, *ETS* Expectation of Treatment Scale, *OTS* Opinion of Treatment Scale.

^a^Waves: screening, baseline, post-treatment (6 weeks for the “face-to-face MBI + TAU” and “TAU alone” or 12 weeks after baseline for the “Internet-delivered MBI + TAU”), post-module (after each individual module for the “face-to-face MBI + TAU” and for the “Internet-delivered MBI + TAU”), follow-ups (both 6 and 12 month follow-up measurements)

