#### Primary outcome

##### *-Beck Depression Inventory II (BDI-II)* [45]

The BDI-II total score, as a continuous variable, will be used as the primary outcome measure at post-test. It has been widely used in clinical research to assess changes in depression severity [20]. Additionally, the BDI-II has shown good sensitivity and specificity in detecting major depressive disorder in the Spanish-speaking population [46]. It is composed of 21 items about symptoms characterizing major depression. The BDI-II total score can be obtained by adding up the answers, from a minimum of 0 to a maximum of 63 points. The BDI-II Spanish version has shown high internal consistency in both general (α = 0.87) and clinical populations (α = .89) [47].

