#### Treatment expectations, opinions, and completion

##### -Expectation of treatment scale (ETS) and opinion of treatment scale (OTS)

These scales are adapted from Borkovec and Nau [61]. They include 5 items, rated from 0 (“not at all”) to 10 (“very much”), that address how logical the treatment seems, to what extent it satisfies the patient, whether it could be used to treat other psychological problems, its usefulness for the patient’s specific problem, and to what extent the treatment might be aversive. The expectation scale will be applied once the treatment rationale has been explained and after M0 to measure subjective patient expectations about the treatment they are about to receive. The opinion scale is administered when the patients have completed the treatment to assess their satisfaction with it.

In the case of the MBI groups, a question will be introduced related to the opinion about each individual module (e.g. “To what extent has this module been useful to you?“), using a visual analogue scale ranging from 0 (“nothing”) to 10 (“very much”), as well as two questions related to reviewing the materials (“Have you reviewed the last module seen in the session and all the materials it includes?”) and homework completion (“Have you done the tasks to train at home?”), with two possible responses (yes vs. no). In addition, a module completion register will be filled out.

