### Main analysis

The efficacy of the “face-to-face MBI + TAU” group compared to the “TAU alone” group will be estimated based on the main BDI-II outcome, which will be considered a continuous variable. Multilevel mixed-effects models will be developed by means of a RM design on an intention-to-treat (ITT) basis, using the restricted maximum likelihood (REML) method, in order to produce unbiased estimates of variance/covariance parameters [54]. Non-standardized slopes and 95% confidence intervals (95% CI) will be calculated by adjusting those variables that show significant differences between groups at baseline. In order to study the specific trajectories of each group throughout the trial and determine whether possible differences between groups are consistent over time, the ‘group x time’ interactions will be calculated. Cohen’s d effect sizes will be calculated at each time point using the combined standard deviation at baseline [64]. Effect sizes are small when d ≤ 0.2; medium when d = 0.5; and large when d ≥ 0.8 [65].

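### The baseline BDI-II is first taken after randomisation and, in the two MBI arms only, after the introductory module M0, so allocation can affect it

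*Protocol article*

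**What the plan says.** Study population, recruitment, and eligibility criteria: after consent, interview and a paper screening survey, "If the participant meets the inclusion criteria, an independent researcher will implement randomization by telephone".

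Interventions, introductory module: M0 covers emotional disorders, the programme's contents and ambivalence about change, and includes a written exercise weighing the costs and benefits of change. On timing: "This module is carried out face-to-face in both treatment conditions before the pre-treatment assessment and the intervention". It is individual for the Internet arm and in a group for the face-to-face arm. No such session is described for TAU patients, who continue with their GP.

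Instruments, Table 1: the BDI-II is scheduled at "Baseline, post-treatment and follow-ups". The PHQ-9 is scheduled at "Screening, post-module, post-treatment and follow-ups", so it is the only depression score with a screening value.

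Treatment expectations, opinions, and completion: "The expectation scale will be applied once the treatment rationale has been explained and after M0". Table 1 lists this scale as a baseline measure.

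The baseline is then used as follows:
- Main analysis: group-by-time mixed model, with slopes estimated "by adjusting those variables that show significant differences between groups at baseline".
- Abstract, Methods: mixed models adjusted for baseline scores.
- Secondary analysis: both BDI-II improvement criteria.
- Cost analysis: effectiveness as baseline minus follow-up BDI-II.
- Sample size: planning "with a common mean at baseline of 22".

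The BDI-II total score "will be used as the primary outcome measure at post-test".

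**The concern.** A baseline taken before randomisation cannot depend on the arm. One taken afterwards can. Here the MBI patients have met the programme and worked through a motivational exercise before they first complete the BDI-II, and the TAU patients have not. Participants are not blind and the BDI-II is answered by the patient, so blinding the baseline assessor does not remove the exposure.

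Any difference between arms that arises this way enters each analysis that subtracts or adjusts for baseline. It could also trigger covariate adjustment under the Main analysis rule. And it would blur the planned baseline comparison, which is meant to check randomisation but would partly test M0.

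**Working it through.** **Order of events.** Randomisation follows screening. M0 precedes the pre-treatment assessment, and its format depends on the arm, so allocation is already known. The Abstract and Study design use the term pre-treatment for the first wave of outcome measurement, so it does not mean the expectation scale alone. That scale, another baseline item, is placed after M0. No passage puts the BDI-II before randomisation. The order is inferred by joining sections, but nothing in the text contradicts it.

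**The plan's own figure.** Inputs from Sample size: means over four waves of 22/16/15/14 (face-to-face), 22/17/16/15 (Internet) and 22/19.5/18.5/17.5 (TAU); SD 5; correlation 0.6 with decay 0.35; two-sided 5%; 33 per arm. A simulation of the group-by-time test with Greenhouse-Geisser correction gives 81% power, which reproduces the planned 80%.

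**Effect of a shift on the main comparison (face-to-face versus TAU, post-test).** Let s be the fall in the MBI baseline mean caused by M0 or by knowing the arm, with the post-test means unchanged. The protocol gives no value for s, so 0.5 and 1 are assumptions. The article describes both a repeated-measures interaction and baseline adjustment, so both are shown.

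- Completers: 40 less 20% = 32 per arm, so √(2/32) = 0.25 and there are 62 degrees of freedom.
- Change contrast: estimate 3.5 − s; SD 5 × √(2 × (1 − 0.6)) = 4.47; standard error 4.47 × 0.25 = 1.12.
- Baseline-adjusted contrast: the slope is 0.6 with equal SDs, so the estimate is 3.5 − 0.6s; residual SD 5 × √(1 − 0.6²) = 4.0; standard error 1.0.

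Power from the noncentral t distribution:

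| s | Change: estimate | Power | Adjusted: estimate | Power |
|---|---|---|---|---|
| 0 | 3.5 | 87% | 3.5 | 93% |
| 0.5 | 3.0 | 75% | 3.2 | 88% |
| 1 | 2.5 | 60% | 2.9 | 81% |

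Power drops below 80% at s = 0.32 for the change contrast and at s = 1.09 for the adjusted one. If the MBI baseline rose by 1 point instead (s = −1), the estimates would be 4.5 and 4.1, overstating the true 3.5.

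**Analyses that avoid the post-M0 baseline.**
- Unadjusted post-test: the estimate stays at 3.5 whatever s is; standard error 5 × 0.25 = 1.25; power 79%.
- Post-test adjusted for the screening PHQ-9, with assumed correlation r: residual SD 5 × √(1 − r²). For r = 0.3 this is 4.77 and power is 82%.

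**The case against.** The strongest reply is that the harm is hypothetical. M0 gives information and one exercise, is placed before the intervention proper and contains no mindfulness practice. The plan expects the whole face-to-face programme to lower the BDI-II by 6 points (22 to 16), so a 1-point shift credits an introduction with one sixth of that. With baseline adjustment, power holds above 80% up to about 1.1 points. All of this stands, and it limits the weight of the point.

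Two stronger readings are tempting.

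- A reader might infer that the trial loses most of its power. In the three-arm test used for the sample size, falls of 0.5, 1 and 2 points in both MBI arms do take power from 81% to 65%, 45% and 17%. But the main analysis compares face-to-face with TAU, where the loss is smaller, and no passage supports a 2-point shift.
- A reader might infer that the design produces false claims of benefit. With no true difference at post-test, a 1-point shift would raise the rejection rate from 5% to about 15% (change) or 9% (adjusted), at 33 per arm by normal approximation. If M0 lowers scores, those extra rejections point towards apparent harm. False benefit needs M0 to raise BDI-II scores, and the document does not suggest that it does.

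The remedy can also create a problem. Screening is on paper, whereas Randomization and blinding has the Internet arm complete all measures online. Simply moving the BDI-II to screening could add a paper-to-online switch in that arm alone. This is a fair objection and the fix has to deal with it.

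Finally, the text on the introductory session is loose. One paragraph describes a group session for both MBIs, while the M0 paragraph says individual for the Internet arm. On either reading only the MBI arms receive it. Fig. 1 is not available here.

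**Conclusion.** The point holds as a structural weakness. As written, the baseline BDI-II comes after allocation and, in the MBI arms only, after M0, so it lacks the protection of randomisation. A shift of s points biases the change contrast by s and the baseline-adjusted contrast by about 0.6s. An unadjusted comparison at post-test, the stated primary time point, is untouched.

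The document fixes neither the size nor the sign of s, so it does not show that the trial is biased, nor in whose favour. The power figures rest on the protocol's SD of 5, correlation of 0.6 and 20% dropout, and on the assumed shifts. The change is worth making because it is cheap and recruitment was still open at publication, not because serious harm has been shown.

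**What to change.** 1. For patients still to be recruited, collect the BDI-II and the other baseline outcomes at the screening visit, before telephone randomisation and before M0. Leave only the expectation scale after M0.
2. Use the same mode for the baseline BDI-II as for later assessments. Failing that, use one baseline mode in all arms and record it, so that a mode switch confined to the Internet arm does not go unnoticed.
3. Record for each patient whether the baseline was taken before randomisation or after M0.
4. Keep the repeated-measures main model, and add one sensitivity analysis of post-test BDI-II that does not use the post-M0 baseline, either unadjusted or adjusted for the screening PHQ-9.

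Cost: a slightly longer screening visit, a short amendment, a somewhat older baseline while groups of 6 to 8 are formed, and two baseline timings within one trial. No extra patients are needed. The sensitivity analysis has about 79% to 82% power at 32 per arm for r between 0 and 0.3. A low r is plausible because eligibility restricts the PHQ-9 to 5–14.

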##### M1. Getting to know mindfulness

This module will show what mindfulness is, prejudices about it, inattention problems in our society, some mindfulness benefits, and recommendations for practicing it. In this module, participants will perform the raisin mindfulness exercise, which is widely used as an introduction to mindfulness meaning.

##### M2. Establishing formal and informal practices

This module will explain the importance of formal and informal practice. To do so, different techniques such as the three-minute practice will be demonstrated.

##### M3. Thoughts management, body scan practice, and values

This module aims to show the importance of thoughts and values in our emotions and lives, and the need to recognize them. It will also include the body scan practice.

##### M4. Self-compassion and integrating mindfulness in everyday life

This module works on how to establish a mindfulness practice habit in order to consolidate the use of this technique. It will also include a self-compassion practice, which has shown its efficacy in treating depression symptoms [10, 33].

These modules can be done step-by-step. When a patient has finished a module, it can be reviewed as many times as necessary. Each module includes: content explanations, self-assessment questions to test whether participants have understood the contents, exercises to practice, and homework assignments.

#### Treatment as usual (TAU)

Participants in the treatment as usual (TAU) arm will continue to be treated by their GPs in their corresponding health centers. The treatments offered by the GPs are mainly pharmacological, with antidepressants and/or anxiolytics being the most frequent medications. In cases of suicide risk or other severe symptoms or unexpected effects during the study, the patient will be referred to specialized mental health care services and excluded from the data analysis.

